### Intervention

Preterm newborns who meet the inclusion criteria will be exposed to a specific, in terms of content and exposure timing, live singing intervention four times in a calendar week – once per day. The decision to implement the intervention four times per calendar week was informed by a critical framework evaluation of clinical and practical constraints outlined in Dimitropoulos [90]. According to this evaluation, conducting the intervention more frequently (e.g., 5 times/week or more) could induce excessive stress on infants and caregivers, raising ethical concerns and logistical challenges for maintaining caregiver involvement within the hospital setting beyond one week. Conversely, a lower frequency (e.g., 3 times/week or fewer) is not feasible due to the study’s design, which explicitly involves four distinct facilitator profiles (mother, father, male music therapist, female music therapist). In addition, by conducting the intervention in the proposed way, we expect to observe and record the immediate and short-term neurophysiological effects of the musical stimuli on the infants’ brains, while ensuring that the data reflects the true impact of the intervention, free from external variables that might arise from a more prolonged or sporadic schedule. Furthermore, the specific exposure over this consistent period will facilitate a comprehensive understanding of any cumulative or evolving effects of the intervention across consecutive sessions, allowing for a detailed analysis of the EEG baselines recorded each one of the four times the intervention is delivered.

Most importantly, we aim for the experimental intervention to be always conducted under specific conditions to ensure consistency and optimize the infants’ response to the musical stimuli. More specifically, the intervention will be delivered post-feeding, at least 30 minutes but not more than 60 minutes after. We believe for this timing to be crucial to ensure that the infants are neither too full nor too hungry, both of which could cause discomfort and impact the infant’s ability to remain calm and attentive during the intervention. Feeding influences the infants’ physiological state significantly [91], and selecting this window helps to maintain a stable state, reducing the likelihood of confounding factors related to digestion or hunger that might affect neural responses. Indeed, previous research supports the importance of carefully timing interventions to coincide with naturally occurring alert behavioral states in preterm infants [92,93]. In this context, to ensure optimal attentiveness, infant behavioral states are closely monitored prior to each session, and interventions are initiated only when infants exhibited a quiet alert state at the minimum, defined by lead physicians and nurses as having open eyes, minimal motor movements, and clear responsiveness to gentle external stimuli.

In addition, any other caregiving activities, including kangaroo care (skin-to-skin contact), will be minimized (following the lead physician’s directions) for at least 15–20 minutes prior to the intervention, with the exception of necessary medical care. This precautionary approach aims to minimize potential satellite processes associated with caregiving that could inadvertently lead to overstimulation or physiological stress. Specifically, these concerns include inadequate thermoregulation potentially causing overheating or chilling, compromised respiratory function due to positioning, accidental dislodgment of critical medical devices, mild fluctuations in heart rate or blood pressure, and caregiver anxiety or suboptimal handling, all of which may impact arousal levels and influence the basal neural activity recorded by EEG [94,95]. By ensuring a period of relative rest before the intervention, we aim to create a consistent starting point for all participants, thereby improving the accuracy and reliability of the neurophysiological data collected. Finally, it should be also noted that the facilitators’ order of intervention delivery for each infant will be changed between participants to achieve better randomization and to avoid potential confounding variables due to a set order of intervention delivery.

As far as the live singing intervention’s structure is concerned, this will take place in two main singing stages complemented by three distinctive blocks of silence, before, between and after each sung session as shown in the following list.

* 180 seconds of silence (*Silence1; Baseline1*)1st singing stage: Signing the specific Note A, repeated *ad libitum* for a total of 60 seconds. (*NoteA*)* 180 seconds of silence (*Silence2; Baseline2*)2nd singing stage: Singing an original song (please see S2) suitable for the NICU environment in terms of structure, acoustic information composition, and volume level (dB), with a total duration of 90 seconds. (*Song*)* 180 seconds of silence (*Silence3; Baseline3*)

We decided to include the two different musical stimuli – the note A and the lullaby song – in order to differentiate between the effects of a simple, consistent auditory stimulus and a more complex, emotionally rich stimulus. Note A represents a controlled and repetitive sound, allowing us to observe basic auditory processing in the infants’ brains. The lullaby, on the other hand, is a complex acoustic stimulus designed to mimic a natural caregiving experience, thereby engaging additional cognitive and affective neural processes. By comparing these two types of stimuli, we aim to understand how different levels of auditory complexity impact neurodevelopmental outcomes.

We furthermore decided to introduce the periods of silence before and after each singing stage to facilitate a return to the baseline of brain activity between the two singing stages, as well as to reduce the potential impact of any residual neural activity from the previous stage. This approach will enable us to achieve a more accurate assessment of the effects of each individual singing stage, and it will also allow for a clearer comparison of the developmental trajectory of the EEG baselines. By incorporating these controlled intervals of silence, we aim to isolate the neurophysiological effects specific to each condition, thus providing a more precise understanding of how the infants’ brain activity evolves over the course of the intervention conditions as well as sessions.

In regard to the singing stages, as stated above, all facilitators will be asked to sing at the same distant location from the cot, maintaining in this way consistent spatial sound parameters of stimulus delivery. For the first stage of the singing part (NoteA), each facilitator will be given a tuning fork (a forked acoustic component that produces sound upon impact and quickly silences) tuned to the musical note A (440 Hz) and asked to sing based on its produced sound the musical note A as best as they can. All facilitators will need to repeat the specific note *ad libitum* at any possible and convenient to them frequency that corresponds to this specific note (i.e., A2: 110 Hz; A3: 220 Hz; A4:440 Hz; A5:880 Hz) over 60 seconds at this stage. The tuning fork has been chosen to be used as it is a safe acoustic accessory for accurately reproducing the tone the facilitator needs to hear as an acoustical template when inserting it into their ear, ensuring at the same time that the infant will not be able to hear it and be affected by it.

For the second singing stage (Song), each facilitator will need to sing *a cappella* a complex acoustic stimulus with organized sounds in the form of a lullaby, specifically created and composed for the study by a professional musician and music therapist (a member of the research team). This lullaby was aimed to have a unique structure and acoustic information composition adhering to the known scientific evidence related to infants’ sound and music perception capabilities [96,97]. The song lasts 90 seconds and features a soft melodic line, gentle rhythm, simple harmonies in a minor key, and soft vocal timbre, influenced by folk characteristics found in Greek lullabies. Its tempo is expected to be approximately 60–75 beats per minute, following the rhythm of the seconds hand of the clock found on site as best as possible for consistency of delivery.

Finally, to ensure the best possible implementation of the intervention – particularly regarding the singing process – all parents of participants who meet the study’s inclusion criteria will receive 30 minutes of training before the actual intervention. This training will be conducted by a member of the research team who is a professional musician, singer, and music therapist. This pre-intervention session aims to equip parents with the necessary skills and understanding to enhance the intervention’s effectiveness, ensuring close consistency among the different facilitators. Additionally, the training session is designed to provide a calming influence on the parents, which can reduce stress and anxiety for both the infants and their caregivers during the delivery of the intervention. We believe that this pre-intervention training will empower parents as active participants in their child’s care, improving adherence and contributing to a more supportive and therapeutic environment throughout our study in the NICU.

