**Fig 2 pone.0328211.g002:**
[figure not shown]
Study Protocol Flow Chart.

In this design, although the EEG will be the primary tool of data collection and analysis, the rationale for incorporating video data is multifaceted. Firstly, the video recordings will complement the electroencephalogram (EEG) recordings in offering a comprehensive parallel view of the infants’ neural and behavioral responses. Furthermore, the videos will serve as a tool for quality control by ensuring that the prescribed research protocol is uniformly followed by all facilitators, contributing to the scientific integrity of the research. Finally, the videos will allow for a later examination of any synchrony or coordinated interactions between the infant and the facilitator, shedding light on phenotypical – not able to be measured by the EEG – aspects of the intervention.

The live singing intervention will be delivered by four different profiles of individuals-facilitators: a male music therapist, a female music therapist, the mother, and the father of the newborn. During the delivery of the intervention (explained in more detail below), there will be five ‘conditions’ measured: Silence1 (180 seconds), Note A (60 seconds), Silence2 (180 seconds), Song (90 seconds) and Silence3 (180 seconds).

It is important to note that the study protocol will be conducted in a dedicated room, largely isolated from the ambient noise typically found in the rest of the NICU. This aspect of the study design is crucial for two main reasons:

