**Fig 5 pone.0328211.g005:**
[figure not shown]
Interaction Plot of Delta Spectral Power by Condition and Facilitator. This figure illustrates the mean delta spectral power (y-axis) across five experimental conditions – Silence1, NoteA, Silence2, Song, and Silence3 (x-axis) – for the four facilitators ([name], Mother, Father, and [name]). Error bars represent the standard deviation (SD) of individual measurements, highlighting the variability of infants’ responses within each facilitator’s group.

More specifically, we realized that mostly during the ‘NoteA’ condition (as also observed in most of the other conditions), there was a significant increase in Delta Spectral Power for the ‘mother’ facilitator, while surprisingly, the ‘Song’ condition showcased the highest impact particularly for the ‘father’ facilitator. As far as the ‘female music therapist ([name])’ facilitator is concerned, the most stable and lowest Delta Spectral Power across all conditions was observed, indicating a consistent but minimal impact, while the ‘male music therapist ([name])’ facilitator showed moderate variability with minor peaks during the ‘NoteA’ and ‘Song’ conditions. Please note here, that especially for the ‘Song’ condition, the ‘male music therapist ([name])’ facilitator ranked second in impact after the ‘father’ facilitator. To further clarify these specific differences, post-hoc comparisons using the Least Significant Difference (LSD) test were conducted as previously decided, revealing that Delta brain activity was significantly higher with the ‘Mother’ facilitator compared to ‘[name]’ (M = 575.92, *p* = 0.002), ‘[name]’ (M = 409.96, *p* = 0.025), and ‘Father’ (M = 313.55, *p* = 0.085) – although for this latter coming quite close to being significant. Additionally, the ‘NoteA’ condition elicited significantly higher brain activity than the ‘Silence2’ condition (M = 470.26, *p* = 0.022) and showed close trends towards significance when compared to the ‘Silence1’ (M = 323.06, *p* = 0.112) and ‘Song’ conditions (M = 362.86, *p* = 0.075).

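### Note A always precedes the lullaby, so the comparison meant to show an effect of auditory complexity cannot be separated from position in the session

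*Protocol article*

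**What the plan says.** The Intervention section explains why both a sustained note and a lullaby are used: "By comparing these two types of stimuli, we aim to understand how different levels of auditory complexity impact neurodevelopmental outcomes". The Study design section lists the blocks of a session as "Silence1 (180 seconds), Note A (60 seconds), Silence2 (180 seconds), Song (90 seconds) and Silence3 (180 seconds". The Intervention section repeats this order and fixes the place of each stimulus: "For the first stage of the singing part (NoteA), each facilitator will be given a tuning fork" and "For the second singing stage (Song), each facilitator will need to sing". What varies is who sings on which day: the facilitators' "order of intervention delivery for each infant will be changed between participants to achieve better randomization", with the stated purpose of avoiding confounding by a set order.

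The silences are included "to facilitate a return to the baseline of brain activity between the two singing stages". Their second stated purpose is to lessen, not to eliminate, what the earlier stage leaves behind.

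Under Outcomes and statistical analysis, the mixed model has condition and facilitator as fixed effects and infant as a random effect. Under Primary outcomes, Note A "showed close trends towards significance when compared to the" Silence1 and Song blocks; for Song the difference is 362.86 with p = 0.075. The Challenges and limitations section does not mention stimulus order.

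**The concern.** A difference between Note A and Song is to be read as the effect of simple versus complex sound. If one stimulus always comes first, that difference also contains whatever else changes between the first and second singing stage: arousal, habituation, time since feeding, and anything left over from the first stage.

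The article itself makes such changes plausible. It describes these infants' physiological and EEG states as unstable (EEG tool section) and says arousal influences basal EEG activity (Intervention section). A quiet alert state is required before a session starts; no re-check before the lullaby is described.

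The protocol guards against this kind of bias for facilitators by varying their order, but not for stimuli. At stake is one stated aim, in an article offered as a methodological template.

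**Working it through.** **The article's own figures.** Both figures that involve condition reproduce.
- Sample size (Table 1): λ = f²·N·m·ε/(1−ρ) = 0.35² × 14 × 5 × 0.75/0.5 = 12.8625. With df (5−1) × 0.75 = 3 and 3 × 13 = 39, power is 0.827 (stated 0.83).
- Note A minus Song: from the Table 3 means, 647.105 − 284.243 = 362.86. With residual variance 404,270.98 and 20 observations per condition (5 infants × 4 facilitators), SE = √(2 × 404,270.98/20) = 201.06. On 88 df, p = 0.075, as reported.

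The problem is therefore bias, not precision or arithmetic.

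**Timetable.** Note A starts at 180 s. Song starts at 180 + 60 + 180 = 420 s. The gap is 240 s in every session.

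**Aliasing.** Let c be the effect of the condition and π the effect of its position among the five blocks. In the fixed sequence Note A is always block 2 and Song always block 4, so

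E(Note A) − E(Song) = (c_Note − c_Song) + (π₂ − π₄).

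Only the sum can be observed. For 14 infants × 4 sessions = 56 sessions, the design matrix with an intercept, 4 condition columns and 4 position columns has rank 5 of 9, and the position-adjusted Note A − Song contrast is not estimable. A position term added to the model would not help under this design.

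**Does varying the facilitators help?** No. Every facilitator follows the same internal sequence, so π₂ − π₄ enters each session with the same sign and does not cancel.

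**What swapping does.** If half the sessions had Song in block 2 and Note A in block 4, the average of the two orders would be

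½[(c_Note − c_Song) + (π₂ − π₄)] + ½[(c_Note − c_Song) − (π₂ − π₄)] = c_Note − c_Song.

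The rank rises to 6 and the contrast becomes estimable with the same N.

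**Sensitivity in the preliminary data.** Subtracting the silence before each stage gives (647.1 − 324.0) − (284.2 − 176.8) = 215.7. With SE = √(4 × 404,270.98/20) = 284.3, p = 0.45. The apparent effect thus shrinks from 362.9 to 215.7 according to how time in session is handled. With five infants this illustrates the dependence; it does not estimate the bias.

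**The silences as evidence of drift.** The means are 324.0, 176.8 and 480.3. Silence1 − Silence2 = 147.2 (p = 0.47), Silence3 − Silence2 = 303.4 (p = 0.13), Silence3 − Silence1 = 156.2 (p = 0.44). These neither show nor exclude drift.

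**The case against.** The protocol does not ignore carry-over. It puts 180 s of silence between the stages, limits caregiving before the session and starts only in a quiet alert state. Pooled delta power in Silence2 (176.8) is below that in Silence1 (324.0), so nothing suggests that a Note A elevation persists into Song. This stands as far as carry-over goes. It does not touch effects of time in session, and the article claims only to reduce residual activity.

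The data also allow a model-based separation: change from the preceding silence, or one pooled silence level plus a linear or quadratic time trend (both full rank: 4 of 4 and 5 of 5 columns). That is correct. But each rests on an untested assumption: that the preceding silence captures the position effect, or that the silences are equivalent and drift is smooth. The article describes neither analysis.

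The study is exploratory, and its primary question and H1 compare facilitators. Facilitator order is varied and stimulus position is the same for all four, so the main inference is untouched. This stands and limits the severity.

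Two stronger readings are tempting, and the documents do not support them.
- A reader might infer that the Discussion's emphasis on the father's voice during the lullaby is a late-session artefact. That comparison is between facilitators within Song, all at the same position after the same sequence, so a late-session state common to all sessions cannot produce it.
- A reader might take the 480.3/176.8 = 2.7-fold spread of the silence means as proof of drift as large as the stimulus effect. That spread depends on Silence3, which follows both stimuli. On the model's scale the widest gap (303.4) is smaller than Note A − Song (362.9), and no pairwise silence contrast is significant.

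**Conclusion.** The point holds for the Note A versus Song contrast only. As designed, this contrast is completely aliased with position in the session and any residual carry-over. That follows from the fixed sequence and does not depend on the preliminary data. More infants would estimate the mixture more precisely without separating it; separation would need one of the untested assumptions above.

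The size of the bias is unknown, and five infants cannot supply it. The sample-size calculation and comparisons between facilitators within a condition, including father versus the others during Song, are not affected.

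Severity is moderate: one stated secondary aim cannot be answered as planned, while the primary question can.

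**What to change.** **For infants still to be enrolled.** Counterbalance the two singing stages between infants from a list made in advance, note-first or lullaby-first. Keep the order constant across one infant's four sessions, so that facilitator contrasts stay within one order. Keep all blocks and durations. Add a singing-position term (first or second stage) to the model.

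**Cost.** A protocol amendment and an allocation list, with no extra recording time, and 1 df. Balance will be only partial, because infants already recorded have one order, so order is partly tied to enrolment period. With n₁ note-first and n₂ lullaby-first infants, the variance of the position-adjusted contrast is (σ²/4)(1/n₁ + 1/n₂), where σ² is the between-infant variance of the infant's mean Note A − Song difference. Assume that only the five reported infants have been recorded and nine of the 14 remain. Then 9 versus 5 gives 0.0778σ² and 10 versus 4 gives 0.0875σ², against σ²/14 = 0.0714σ² when balanced. The standard error is about 4% to 11% larger. Counterbalancing does not remove unequal carry-over, and the 60 s versus 90 s difference in duration remains.

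**For infants recorded in the fixed order, or if the order is not changed.** Withdraw the complexity interpretation of Note A versus Song, including the p = 0.075 trend, and state the order confounding under limitations. This needs only a change of text.

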### Protocol amendments

The study protocol reported here is the second configured version, following several adjustments made for both practical and scientific purposes. An evaluation process was carried out in line with established medical research guidelines [98] and the findings informed a series of recommendations, which were incorporated into the current study design. A detailed account of the evaluation process as well as the changes made from the original protocol are available in Dimitropoulos [90] in full, and briefly in S3.

### Outcomes and statistical analysis

To rigorously evaluate the effects of our live singing intervention, we decided to employ a series of advanced statistical methods tailored to the specificities of the study design and data characteristics. The complete analysis focused on the EEG-based outcome measures, with an emphasis on Spectral Power (primary outcome) and Spectral Entropy (secondary outcome), across the Delta frequency band.

Special attention was given to the Delta frequency band as it is widely recognized for its relevance in neonatal brain activity [99–100]. The Delta frequency band, typically ranging from 0.5 to 4 Hz, is the slowest of the EEG frequency bands and is a critical marker of brain maturation. Higher absolute power in the delta frequency band has been associated with more favorable long-term neurodevelopmental outcomes, reflecting the progression of underlying neural processes during early development [99]. Given its prominence in this context, we believe that the Delta frequency band can be an essential marker for assessing the impact of sound and music on the neurophysiological state of our participants, providing in result critical insights into how these infants process auditory stimuli and the extent to which our intervention influences brain activity patterns.

More specifically to the design of our statistical analysis process and given the study’s repeated measures design and the nested data structure (with multiple observations per infant), a mixed-effects model was decided to be employed to analyze first the Delta Spectral Power, allowing for the inclusion of both fixed effects (conditions and facilitators) and random effects (variability across individual infants), while also meticulously fitting the model to account for the inter-individual variability after isolating the impact of the different intervention conditions and facilitator profiles.

Specifically, to the Spectral Power approach, we decided to focus on this continuous measurement EEG feature as it can provide information about the intensity and prevalence of different types of neural oscillations [101] and it can help us better understand how the fluctuating premature infant brain activity changes over time. The thorough statistical analysis approach we propose here on the Delta Spectral Power is expected to generate fixed and random effects estimates, while to further elucidate the specific differences between condition/facilitator combinations, a Least Significant Difference (LSD) post-hoc test will be also conducted on the model’s outcome, aiming to identify which specific pairs of conditions or facilitators exhibit significant differences in brain activity, despite the increased risk of Type I errors due to multiple comparisons.

Parallel to the analysis of Delta Spectral Power, a similar mixed-effects model will be applied to the Delta Spectral Entropy data collected, following the same consideration for random and fixed effects, and aiming to explore how variations in spectral entropy, influenced by the different intervention profiles, reflect the neurophysiological responses of the infants. We decided to further study the EEG feature of Spectral Entropy in this context as it can offer a different dimension of analysis compared to Spectral Power and reflect in more detail the overall organization and complexity of the oscillations studied through the Delta Spectra Power approach. More specifically, Spectral Entropy is considered a measure of the complexity or irregularity of a signal’s frequency distribution [102], quantifying the degree of disorder or unpredictability within the power spectrum of a specific signal – in our case the Delta frequency band. A decrease in Spectral Entropy could indicate a transition to more synchronized and less complex neural activity, while conversely, higher Spectral Entropy might suggest more distributed and diverse neural activity, which could be linked to alertness or cognitive engagement.

Infusing this extra step of statistical analysis on our collected EEG data may be proved particularly valuable because it may reveal subtle changes in brain activity that may not be apparent through power analysis alone. As with the Spectral Power analysis, and subsequent to the mixed-effects model for Delta Spectral Entropy, a Least Significant Difference (LSD) post-hoc test will be also employed to investigate the differences between condition/facilitator combinations as in the previous approach.

